## Abstract

**Background:**

Undiagnosed airflow limitation is common in the general population and is associated with impaired health and functional status. Smoking is the most important risk factor for this condition. Although primary care practitioners see most adult smokers, few currently have spirometers or regularly order spirometry tests in these patients. Brief medical advice has shown to be effective in modifying smoking habits in a large number of smokers but only a small proportion remain abstinent after one year. The aim of this study is to evaluate the effectiveness of regular reporting of spirometric results combined with a smoking cessation advice by a primary care physician on smoking quit rate in adult smokers.

**Methods/design:**

Intervention study with a randomized two arms in 5 primary care centres. A total of 485 smokers over the age of 18 years consulting their primary care physician will be recruited.

On the selection visit all participants will undergo a spirometry, peak expiratory flow rate, test of smoking dependence, test of motivation for giving up smoking and a questionnaire on socio-demographic data. Thereafter an appointment will be made to give the participants brief structured advice to give up smoking combined with a detailed discussion on the results of the spirometry. After this, the patients will be randomised and given appointment for follow up visits at 3, 6, 12 and 24 months. Both arms will receive brief structured advice and a detailed discussion of the spirometry results at visit 0. The control group will only be given brief structured advice about giving up smoking on the follow up. Cessation of smoking will be tested with the carbon monoxide test.

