### Study design and setting

Interventional study with two randomized arms in 5 primary care centers of two health areas in the Maresme region (Catalonia, Spain). A total of 392 smokers over the age of 18 years consulting their primery care physician will be recruited.

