#### Sample size and selection method

To carry out the main objective of the study, sample size calculation will be performed according to the following parameters: detection of a difference greater than or equal to 10% between the two groups in regard to smoking cessation, a proportion of 5% of smoking cessation in one of the groups accepting an alpha risk of 0.05 and a beta risk of 0.10 in a bilateral contrast, 187 smokers are required in the control group and 187 smokers in the intervention group. It is assumed that 5% of smokers will withdraw the study.

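### The abstract plans to recruit 485 smokers and the methods 392; the sample-size paragraph supports 392 to 394 and gives no basis for 485

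*Protocol article*

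**What the plan says.** The protocol article gives a recruitment total in two places.

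- Abstract, Methods/design: "A total of 485 smokers over the age of 18 years consulting their primary care physician will be recruited".
- Study design and setting: "A total of 392 smokers over the age of 18 years consulting their primery care physician will be recruited".

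The section Sample size and selection method does not print a total after loss, but it gives everything needed to reach one. The trial is sized on "detection of a difference greater than or equal to 10% between the two groups in regard to smoking cessation". The reference rate is "a proportion of 5% of smoking cessation in one of the groups". Alpha is 0.05 two-sided and beta is 0.10. The result is that "187 smokers are required in the control group and 187 smokers in the intervention group", followed by the statement "It is assumed that 5% of smokers will withdraw the study".

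**The concern.** Apart from the number and a spelling slip, the two recruitment sentences are the same: same population, same setting, same verb. One therefore cannot be read as the number approached or screened and the other as the number randomised. The article gives two values for one design parameter.

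The recruitment total tells the reader when enrolment is complete. With two values in print, a final count of, say, 430 could be called an overrun of the methods figure or a shortfall from the abstract figure. The abstract is also the part of the article most readers see, so the figure most likely to be repeated is the one the sample-size paragraph does not support.

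**Working it through.** **Inputs**, all from Sample size and selection method: cessation of 5% in one group; a difference of at least 10 percentage points, hence 15% in the other group; two-sided alpha 0.05 (z = 1.960); beta 0.10 (z = 1.282); 187 per group; 5% withdrawal. The two recruitment totals come from the abstract (485) and from Study design and setting (392).

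**Step 1: reproduce the 187.** Two-proportion formula with pooled variance under the null hypothesis and no continuity correction, mean proportion 0.10:

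n = [1.960 x sqrt(2 x 0.10 x 0.90) + 1.282 x sqrt(0.05 x 0.95 + 0.15 x 0.85)]² / 0.10²

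= [1.960 x 0.4243 + 1.282 x 0.4183]² / 0.01 = (0.8315 + 0.5361)² / 0.01 = 187.05 per group.

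Strict rounding up gives 188. At the stated 187 the power is 0.8999. The 187 is therefore reproduced, and it is the number before any allowance for loss. The base is 2 x 187 = 374.

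**Step 2: add the stated 5% loss.**

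- Multiplying: 374 x 1.05 = 392.7, which truncates to 392. Per group, 187 x 1.05 = 196.35, taken as 196, and 2 x 196 = 392.
- Dividing: 374 / 0.95 = 393.7, so 394, or 197 per group.

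Dividing is the exact way to be left with 374 after 5% loss. The two conventions differ by two participants.

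**Step 3: look for a route to 485.** The most generous common variant, the continuity-corrected formula, gives 207 per group. That is 414 in all, and 414 / 0.95 = 435.8, so 436, still 49 short of 485. Unpooled variance (184 per group) and the arcsine method (178 per group) give smaller numbers than the plan's own. None of these variants reaches 485 from the stated inputs.

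**Step 4: power at each total**, for 5% against 15%, by the normal approximation that matches step 1:

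power = Φ{[0.10 x sqrt(n) − 0.8315] / 0.4183}, with n per group.

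| Recruited | Power, no loss | Left per group after 5% loss | Power after 5% loss |
|---|---|---|---|
| 392 | 91.3% | 186.2 | 89.9% |
| 394 | 91.4% | 187.15 | 90.0% |
| 485 | 95.9% | 230.4 | 95.0% |

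**Step 5: size of the contradiction.** 485 − 392 = 93, and 93 / 392 = 23.7%.

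**The case against.** The strongest reply is that the body of the article is consistent. Study design and setting and the sample-size paragraph agree with each other, the odd figure is in the abstract alone, and it errs on the high side. On the stated assumptions neither total leaves the trial materially underpowered. All of this stands, and it limits the point to a contradiction in the stated total. It does not remove the contradiction, because the article does not say which figure is meant.

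Three stronger readings are tempting, and the document does not support them.

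- *That 392 is also wrong.* It is two short of 394 because 5% was added rather than divided out. The effect on power after loss is 89.9% against 90.0%, which is a rounding convention and not a defect.
- *That the loss allowance and the power are left open.* Both are stated once, without conflict, in the sample-size paragraph, and 392 fits both.
- *That 485 reveals an expected loss of about 23%.* The arithmetic is 1 − 374/485 = 22.9%, but it assumes that 485 was obtained by inflating 374 for withdrawal. The article mentions no loss other than 5%. The figure could equally be a leftover, a misprint, or a number chosen with the peak-flow and COPD-prevalence aims in mind, since the calculation is said to serve the main objective only. None of these origins is documented either. It follows that combining 392 recruited with 23% loss (about 302 left, power about 83%) describes a scenario that the plan does not contain.

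**Conclusion.** The contradiction is real and should be corrected: two recruitment totals, 93 participants apart, with no explanation. The stated inputs lead to 392 to 394 and about 90% power after loss. They do not lead to 485, which would give about 95% after the same loss.

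This rests on reading the 5% as the lower cessation rate with 15% in the other group (a rate 10 points below 5% is impossible), on the pooled two-proportion formula that reproduces the 187, and on equal groups, as the paragraph states. The contradiction itself needs none of these assumptions. Which total was intended cannot be settled from the article. The finding is no evidence that the trial is underpowered or that its withdrawal assumption is wrong.

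**What to change.** State one recruitment total in the abstract and in Study design and setting, and print the same total after loss in the sample-size paragraph so that the chain from 187 per group can be followed.

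- If the stated inputs are what was intended, change the abstract to 392. If the investigators prefer to divide by 0.95, put 394 in both places.
- If 485 is the intended total, correct Study design and setting, and state in the sample-size paragraph the reason for 485 and the power it gives (95.0% if 5% withdraw). The reason should be the one actually used; a withdrawal rate should not be worked backwards from the number.

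The first option costs one number in the abstract, or two numbers and two more participants if 394 is chosen. The second costs one number in the methods and a sentence or two in the sample-size paragraph, and it commits the trial to 93 more participants than the methods now state. Neither changes the design or the analysis.

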**Discussion:**

Early identification of functional pulmonary abnormalities in asymptomatic patients or in those with little respiratory symptomatology may provide "ideal educational opportunities". These opportunities may increase the success of efforts to give up smoking and may improve the opportunities of other preventive actions to minimise patient risk. Comparing adult smokers in the intervention group with those in the control group, a minimum improvement expected with respect to the rates of smoking cessation would represent a large number of avoided morbimortality.

**Trial Registration:**

ClinicalTrials.gov: NCT01296295

## Background

Chronic obstructive pulmonary disease (COPD) involves a heterogeneous group of processes characterised by little reversible air flow obstruction of chronic and progressively disabling evolution which causes a high morbimortality around the world. According to the World Health Organisation (WHO) 210 million people around the world have COPD [1] and despite being a potentially avoidable disease, has foreseen that in 2030 COPD will be the cause of 7.8% of all deaths and 27% of the deaths related to smoking only by cancer and cardiovascular diseases [2].

In addition to increasing the mortality, its prevalence is also slowly rising so epidemiological predictions foresee a growing trend in the next decades [3]. These and other reasons have converted this health care problem into a priority in the most important international institutions [4]. In our setting the high prevalence of COPD in parallel with the smoking habit have been consistently emphasised [5]. The IBERPOC study has evaluated COPD among 9% of the Spanish population between 40 to 69 years of age, a percentage that increases up to 23% in subjects over the age of 60 years [6]. At the time of the study, 48% of the population reported some respiratory symptom (13.5% cough, 10.7% chronic expectoration and 10.4% dyspnea) always higher frequency in men.

The diagnosis of COPD is clear and its treatment is feasible. However, a high number of patients remain undiagnosed and therefore not treated. Interestingly, the letters of COPD coincide with "Confusion Over Patient Diagnosis" [7]. In Spain, data of the IBERPOC study confirm that underdiagnosis is frequent (78.1%) and is accompanied by undertreatment (80.7%) [8]. The reasons include not only certain nihilistic attitudes towards treatment but also an initial symptomatology makes diagnosis difficult [9]. The preliminary results of the EPI-SCAN study performed 10 years after the IBERPOC have confirmed the high rate of underdiagnosis of COPD in Spain with a prevalence of 10.2% in the population from 40 to 80 years of age. Underdiagnosis 10 years later was slightly reduced from 78% in the IBERPOC study to 73% in EPI-SCAN. Moreover, undertreatment was reduced from 81% to 54% [10].

From a more economic point of view, the morbimortality associated with COPD has an enormous social and individual impact. It has been estimated that COPD consumes 2% of the Spanish health care budget representing approximately 0.25% of the Gross National Product. A recent study has shown an average annual cost per patient of $ 1,760 [11]. Family practitioners are in the best position to change this scenario.

Aetiopathogenics of COPD are multifactorial. A history of smoking is invariably found in most cases, although 15% to 20% of smokers develop the disease [12]. Thus, the presence of smoking habit and suggestive symptomatology make functional respiratory evaluation compulsary for early detection of respiratory disease obligatory [13]. Forced spirometry is a simple reproducible test and an objective method to quantify airflow obstruction in the early phases. Several studies have reported that forced spirometry in subjects at risk is a highly effective strategy for diagnosis of COPD. Investigators from the University of Maastricht performed this approach in the primary care setting and demonstrated its efficacy [14]. According to this study, the probability of detecting spirometric alterations in smokers over 40 years of age with chronic cough is 2.5-fold greater than in non smokers. Likewise, a multicentre study carried out in 12 primary care centres showed a prevalence of COPD of 30.6% among smokers of 10 packs/year over the age of 40 [15].

The risks derived from smoking are well known in the biomedical community and political class, and increasingly more, by the society in general. The international GOLD (Global Initiative for Chronic Obstructive Lung Disease) consensus insists that smoking is the most important risk factor for the development of COPD and thus, antismoking advice should be the first therapeutic recommendation [16]. However, this obvious objective is not at all easy to achieve. At present, 29% of the European Union population is considered to be a regular smoker. According to the last Health Care Plan of Catalonia, in 1998 the smoking prevalence in the population from 15 to 64 years of age was 37.5% (30.7% in women and 44.4% in men)[17]. The last National Health Survey of 2006 carried out by the Spanish Ministry of Health showed the smoking prevalence was 26.4% over 16 years of age (31.6% in men and 21.5% in women ) with 42% smoking ≥ 20 cigarettes / day (50.2% men and 31.6% women) [18].

Cessation of smoking is the simplest and most profitable preventive method to avoid the development of COPD. It is also the most effective therapeutic intervention in already diagnosed patients and is the only effective method to increase survival [19]. Giving up smoking has an immediate effect on both pulmonary function and the risk of hospitalisation and total mortality [20]. Many studies have shown that smoking cessation produces an improvement in respiratory symptoms and slows the decline in FEV1 in people with COPD [21].

The IBERPOC study reported that almost 70% of the subjects with mild COPD were smokers and many were in the precontemplative phase [22]. Another added problem is relapse of smoking which is of 70% during the first year in the general smoker population. These values are greater in the COPD group [23]. This fight has become a priority in the public health care setting for most governments of developed countries. As early as1986, the WHO agreed that smoking, in any of its forms, was incompatible with its strategic objectives.

Many strategies have been considered to fight smoking and these may essentially be classified into 3 large groups: market regulation, taxation on the price of tobacco, and health protection [24]. The promotion of healthy lifestyles is the most effective and efficient strategy within the public health setting. According to the evidence available, both isolated medical advice as well as therapy with pharmacologic measures, have shown to be effective in the approach towards smoking. The health care costs of treatment, such as a minimum medical intervention or using nicotine substitutes or other drugs, would be lower than resources devoted to other prevalent diseases such as arterial hypertension or hypercholesterolemia. With regard to isolated medical advice, this has shown to be effective in modifying the smoking habit in a large number of smokers, although only a small proportion of these patients remained abstinent after one year [25]. Although these values may vary according to the different studies, the differences found are small and range from a modest 2% described in the review by Law and Tang [26] to 11% achieved by Torrecilla et al [27] in an autochthonous study. According to recently published data, reprinting of air flow obstruction by spirometry together with antismoking advice would increase the percentage of success by 16.5%, compared to using pharmacologic agents [28]. The results obtained may seem to be modest but from a populational point of view any strategy to reduce the consumption of tobacco, regardless of being small in relative terms, is very beneficial in absolute numbers with respect to both avoidable diseases and cost saving in the health system.

The different strategies used to reduce smoking consumption have been evaluated by the Cochrane Library. Biomedical risk as an aid in smoking cessation was assessed and it was concluded that there are few tests on the effects of most of the biomedical tests available to evaluate risks [29]. Spirometry combined with interpretation of the results in relation to pulmonary age presented a significant effect of 13.6% on the rate of smoking cessation in the intervention group at 12 months and of 6.4% in the control group [30].

Indeed, although adequate tools for aiding patients to give up smoking are currently available, the percentages of success may be insufficient if the objective is to achieve a reduction in the prevalence of smoking. It is essential to investigate broad new populational approaches which reduce the magnitude of the problem, particularly when COPD is already present. If it is taken into account that spirometry is a simple and accessible test and that up to 70% of the smokers consult primary care physicians at least once a year, it is logical to assume that the opportunities of the family practitioners to diagnose the disease and offer antismoking advice are high and even more so when the work setting is the ideal place to do this.

## Methods/Design

### Study Objectives

#### Main objective

To evaluate the effectiveness of regular reporting of spirometric results combined with a smoking cessation advice by a primary care physician on smoking quit rate in adult smokers.

#### Secondary objective

To evaluate the validity of the peak expiratory flow rate to detect COPD in adult smokers and determine the prevalence of COPD and the severity of the limitation of airflow in adult smokers attended in primary care.

### Study design and setting

Interventional study with two randomized arms in 5 primary care centers of two health areas in the Maresme region (Catalonia, Spain). A total of 392 smokers over the age of 18 years consulting their primery care physician will be recruited.

### Study subjects

#### Study population

All the adult smoker population over the age of 18 consulting their primary care physician for any reason and who do not fulfil the exclusion criteria.

#### Exclusion criteria

Previous diagnosis of COPD by spirometry. Patients with counterindication to spirometry. Patients without a telephone. Patients with communication difficulties: cognitive and/or sensorial deterioration, language.

Patients with severe disease of poor prognosis (life expectancy less than one year). Patients with another respiratory disease: asthma, neoplasm of the respiratory tract, pulmonary thromboembolism, pulmonary tuberculosis, interstitial diseases. Patients who do not give written informed consent to participate in the study.

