### Analysis plan

To achieve the first objective the rates of withdrawd and reduction of the smoking habit of the two groups will be compared at 6, 12, and 24 months.

To achieve the second objective the sensitivity, specificity and positive and negative predictive values of peak flow compared to spirometry will be determined.

For the third objective, the proportion of COPD and the severity of air flow limitation will be determined according to different study variables (age, sex, smoking habit, symptoms...).

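### The secondary objective promises COPD prevalence in primary care smokers, but excluding smokers already diagnosed by spirometry leaves only previously undiagnosed disease to be estimated

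*Protocol article*

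**What the plan says.** Under Secondary objective, the second half of the aim is to "determine the prevalence of COPD and the severity of the limitation of airflow in adult smokers attended in primary care". Under Analysis plan, the matching third analysis states that "the proportion of COPD and the severity of air flow limitation will be determined according to different study variables", with age, sex, smoking habit and symptoms as examples.

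Under Exclusion criteria, the first item is "Previous diagnosis of COPD by spirometry". Asthma and several other respiratory diseases are also excluded. Study population defines those enrolled as adult smokers "consulting their primary care physician for any reason and who do not fulfil the exclusion criteria".

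No section limits the prevalence objective to new or undiagnosed disease. None plans a count of smokers turned away for known COPD, or a way to add them back.

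**The concern.** The objective names one quantity and the eligibility rule delivers another. Removing people because they have the condition lowers the proportion with the condition among those who remain. The direction is certain whenever at least one smoker is excluded for known COPD and some of those remaining do not have it.

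A figure reported as COPD prevalence in primary care smokers would understate the burden in that group. It would also be read against the prevalences in Background, where IBERPOC "evaluated COPD among 9% of the Spanish population between 40 to 69 years of age" and EPI-SCAN is reported "with a prevalence of 10.2% in the population from 40 to 80 years of age". Severity is open to the same problem: Background says that early symptoms make diagnosis difficult, so diagnosed cases may on average be more advanced, and leaving them out may tilt the distribution towards milder disease.

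This cannot be left to the analysis stage. Objective and eligibility are both stated in the protocol, and no analysis of the enrolled smokers alone can recover people who were not enrolled or counted.

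**Working it through.** **The plan's own figure.** The article gives no expected prevalence, precision or bias for this objective. Its only calculated figure is 187 smokers per arm for cessation (5% versus 15%, two-sided alpha 0.05, power 0.90). A pooled normal approximation gives 188, so that figure reproduces, and it does not depend on this point.

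**Inputs, all from Background**
- Prevalence P: 9% (IBERPOC, general population aged 40 to 69); 10.2% (EPI-SCAN, general population aged 40 to 80); 30.6% (primary care smokers over 40 with a stated pack exposure).
- Undiagnosed share u: 78.1% in IBERPOC and 73% in EPI-SCAN; the article itself says "Underdiagnosis 10 years later was slightly reduced from 78% in the IBERPOC study to 73% in EPI-SCAN". The diagnosed share 1 − u is therefore 21.9% or 27%.
- Share k of diagnosed cases whose diagnosis was by spirometry: not given. I take k = 1, then k = 0.5 as an assumption.

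**Formula.** The share of cases excluded is d = k(1 − u). Excluded cases leave numerator and denominator:

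observed = P(1 − d) / (1 − P·d)

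relative shortfall = 1 − (1 − d) / (1 − P·d)

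Example, EPI-SCAN pair with k = 1: 0.102 × 0.73 / (1 − 0.102 × 0.27) = 0.07446 / 0.97246 = 7.66%, a shortfall of 1 − 0.0766/0.102 = 24.9%.

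| P | u | Observed, k = 1 | Shortfall, k = 1 | Observed, k = 0.5 | Shortfall, k = 0.5 |
|---|---|---|---|---|---|
| 9% | 78.1% | 7.2% | 20.3% | 8.1% | 10.1% |
| 10.2% | 73% | 7.7% | 24.9% | 8.9% | 12.3% |
| 30.6% | 78.1% | 25.6% | 16.3% | 28.2% | 7.9% |
| 30.6% | 73% | 24.3% | 20.4% | 27.6% | 9.8% |

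The shortfall is thus about 16% to 25% if all diagnoses were by spirometry, and about 8% to 12% if half were.

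**Sensitivity.** The article gives no diagnosed share for consulting smokers over 18. If d lay anywhere from 10% to 50% (assumption), the shortfall would run from about 7% (P = 30.6%, d = 10%) to about 47% (P = 10.2%, d = 50%).

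**Adding known cases back.** The obvious repair, (known + new)/(known + tested), is biased if it counts every known case turned away but only those remaining smokers who consent and are tested. Take 1,000 smokers approached, P = 10.2%, u = 73%, all diagnoses by spirometry, and 60% of the others tested (assumption):
- Known cases: 1,000 × 0.102 × 0.27 = 27.5.
- Others: 972.5, of whom 583.5 are tested and 74.5 × 0.6 = 44.7 are found.
- Simple add-back: (27.5 + 44.7)/(27.5 + 583.5) = 72.2/611.0 = 11.8%, which is about 16% above the true 10.2%.
- Consistent version: 44.7/583.5 = 7.66%, applied to 972.5 gives 74.5; (27.5 + 74.5)/1,000 = 10.2%.

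**The case against.** The best defence is that the study is about undetected disease. The abstract opens on undiagnosed airflow limitation, the discussion there speaks of early identification, and Study population openly defines those enrolled after the exclusions. On that view the authors mean undiagnosed COPD, and the exclusion suits a trial that uses spirometry results as motivation. This explains the design but does not mend the text: the objective still names COPD prevalence in adult smokers attended in primary care. The exclusion itself need not change.

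Several limits on the point do stand:
- A reader might infer that the reported prevalence will be one fifth to one quarter too low. The document does not support a firm size. The 73% and 78.1% come from general-population surveys of people aged 40 and over, and are not stated to refer to diagnosis by spirometry. The abstract says few primary care practitioners have spirometers or regularly order the test, so some diagnosed smokers may lack a spirometric diagnosis and remain eligible.
- The 30.6% may not be a total prevalence. The article does not say whether that study counted known cases. Comparison with 9% and 10.2% is in any case limited, because those are not figures for smokers.
- A reader might infer that prevalence cannot be estimated at all. That is true of total prevalence from the enrolled sample alone. The frequency of undiagnosed disease can be estimated, and total prevalence is recoverable with a proper screening count.
- A reader might infer that severe disease is cut off. Severe cases not yet diagnosed stay eligible, and no section gives severity by diagnosis status.
- This is one part of a secondary, descriptive objective, not the trial's main result.

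**Conclusion.** The mismatch is real and is settled by the text. The secondary objective and third analysis claim the prevalence and severity of COPD in adult smokers attended in primary care, while the sample can give only COPD not previously diagnosed by spirometry among eligible smokers. The result is lower than the stated target.

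The size is conditional. The 16% to 25% range requires both that the Background underdiagnosis shares hold for these smokers and that all diagnosed cases were diagnosed by spirometry; the 8% to 12% range requires the same shares and half the diagnoses by spirometry. Both treat 9%, 10.2% and 30.6% as total prevalences. Under-representation of severe disease is plausible but cannot be sized. Excluding asthma and other respiratory disease narrows the population further, with an effect that also cannot be sized.

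The randomised comparison of quit rates and its sample size are not touched. The change should be made, because otherwise a stated objective will be reported under the wrong name.

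**What to change.** Restate the second part of the secondary objective and the third analysis as the frequency and severity of airflow obstruction not previously diagnosed by spirometry among eligible smokers, and do not present the result as total COPD prevalence. This is rewording only; eligibility, visits and sample size stay as they are.

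If total prevalence is wanted, keep a log at the selection visit of all smokers approached (A) and those excluded for known COPD (K). With p the proportion found in tested smokers, report (K + p(A − K))/A, stating the assumption that tested smokers represent all approached smokers without known COPD. Alternatively, count known cases only among smokers who would otherwise be eligible and would consent, so that they match the tested group. Do not divide all known cases plus new cases by all known cases plus those tested.

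The log is a small addition to recruitment. Adding the severity of known cases would cost more, since it needs access to records of people who are not enrolled, and Ethical considerations makes access to clinical histories subject to authorisation and confidentiality rules.
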